## Abstract

**Background:**

Colorectal cancer is the second most common tumor in developed countries, with a lifetime prevalence of 5%. About one third of these tumors are located in the rectum. Surgery in terms of low anterior resection with mesorectal excision is the central element in the treatment of rectal cancer being the only option for definite cure. Creating a protective diverting stoma prevents complications like anastomotic failure and meanwhile is the standard procedure. Bowel obstruction is one of the main and the clinically and economically most relevant complication following closure of loop ileostomy. The best surgical technique for closure of loop ileostomy has not been defined yet.

**Methods/Design:**

A study protocol was developed on the basis of the only randomized controlled mono-center trial to solve clinical equipoise concerning the optimal surgical technique for closure of loop ileostomy after low anterior resection due to rectal cancer.

The HASTA trial is a multi-center pragmatic randomized controlled surgical trial with two parallel groups to compare hand-suture versus stapling for closure of loop ileostomy. It will include 334 randomized patients undergoing closure of loop ileostomy after low anterior resection with protective ileostomy due to rectal cancer in approximately 20 centers consisting of German hospitals of all level of health care. The primary endpoint is the rate of bowel obstruction within 30 days after ileostomy closure. In addition, a set of surgical and general variables including quality of life will be analyzed with a follow-up of 12 months. An investigators meeting with a practical session will help to minimize performance bias and enforce protocol adherence. Centers are monitored centrally as well as on-site before and during recruitment phase to assure inclusion, treatment and follow up according to the protocol.

**Discussion:**

Aim of the HASTA trial is to evaluate the efficacy of hand-suture versus stapling for closure of loop ileostomy in patients with rectal cancer.

**Trial registration:**

German Clinical Trial Register Number: DRKS00000040

## Background

### Background and rationale

Colorectal cancer is the second most common tumor in developed countries, with a lifetime prevalence of 5% [1,2]. Approximately 30% of these tumors are located in the rectum. Surgery forms the cornerstone in the treatment of rectal cancer, with the low anterior resection (LAR) with totally mesorectal excision being the standard procedure [3]. Today, a diverting protective stoma should be used until definite healing of the anastomosis is achieved [4,5]. So far, it remains still uncertain whether a loop ileostomy or a colostomy is preferable [6-8]. After a period of three months the ileo- or colostomy is subsequently closed and intestinal continuity is re-established. Due to the high prevalence of rectal cancer, this is a frequently performed procedure in surgical practice.

### Preliminary data

One randomized controlled trial (RCT) including 141 patients over 6 years has compared hand-sutured and stapled anastomosis for closure of loop ileostomy so far [9]. The results of this trial have shown a significantly higher rate of postoperative bowel obstruction (14% versus 3%, p = 0.0168) for patients who received hand-sutured anastomosis. However, there are severe methodological issues which impair the interpretation of this trial. First, the trial included a heterogeneous group of patients with many different underlying benign and malignant diseases. Second, it was performed in a single-center setting with only a low number of surgeons performing the investigated techniques. Therefore, the results reflect the situation of loop ileostomy closure at this institution rather than practice in general. Third, results of this trial are probably biased by learning curve effects of participating surgeons [10]. The authors report that two-thirds of bowel obstructions observed in the trial occurred in the first half of the study. In addition, all patients requiring re-operations had initial closure of the loop ileostomy performed by senior registrars (as opposed to consultant surgeons). Due to the methodological and clinical limitations of this trial a multi-center pragmatic trial is needed to confirm the observed findings.

### Objectives and hypotheses

The objective of the HASTA-Trial is to investigate whether there is a difference in rate of bowel obstruction one month after hand-suture as compared to stapling loop ileostomy closure. If p_HA_/p_HA _denotes the rate of occurrence of bowel obstruction within one month after ileostomy closure in the hand-suture group (HA)/stapler group (STA), then the following two-sided test problem is assessed: H_0_: p_HA _= p_STA _vs. H_1_: p_HA _≠ p_STA_.

## Methods/Design

### Study population and Trial group

Patients with history of low anterior resection (LAR) and creating of a protective loop ileostomy for rectal cancer who are planned for elective closure of loop ileostomy will be recruited for this trial.

The HASTA-Trial is conducted by a national study group consisting of certified bowel centers and other German hospitals of all level of health care. Trial design and management are under the responsibility of the Study Center of the German Surgical Society, biostatistical planning, data management and analysis is performed by the Institute of Medical Biometry and Informatics, University of Heidelberg.

#### Subject inclusion criteria

• Patients equal or older than 18 years scheduled for elective ileostomy closure after LAR

• Informed consent

#### Subject exclusion criteria

• Pathologic findings in routine preoperative diagnostic tests (e.g. anastomotic leakage) which do not allow a safe ileostomy closure

• Participation in another intervention-trial with interference of intervention and outcome of this study

• Expected lack of compliance

Centers are asked to document potential patients in a screening log. Thus, reasons for exclusion are documented.

### Sample size

The prior assumptions for sample size calculation are based on the results of Hasegawa et al. (2000) ([9]) and assume prevalence rates with respect to the primary endpoint of 3% in the stapler group and 14% in the hand-suture group. To detect this difference with the two-sided chi-square test at a type I error rate of (two-sided) with power, a sample size of n = 133 evaluable patients (treatment and follow up according to the protocol) per group is necessary. It can be expected that taking into account the covariate "skill of surgeon" in the analysis will increase the power as compared to the chi-square test. The drop out rate within one month after index operation is expected to be about 20% overall. Therefore, another total of 68 patients have to be randomized to obtain the required number of evaluable patients. The total sample size to be randomized is therefore 334 patients.

### Randomization and blinding

The randomization numbers will be allocated to the two groups in balanced permuted blocks and stratified by center using the web-based software "Randomizer" provided by the Institute of Medical Informatics, Statistics and Documentation of the Medical University of Graz (http://www.randomizer.at). This software allows choosing different randomization methods as well as different sets of parameters for the chosen method.

To avoid any potential of predicting the group allocation of future patients, the block length is fixed in a separate document that is withheld from the study site. In addition, persons with the right to randomize with the software described above do not have the right to read or edit the randomization design chosen within the software. The software stores the result of randomization and patient characteristics as well as the name of the person who randomized and the randomization date in a separate file, and only authorized persons can download this file. Patients are randomized the day before or on the day the surgical intervention is performed.

Patients are not blinded and blinding of the surgeon is unfeasible. Typical symptoms for the primary outcome, bowel obstruction, like productive vomiting, gastric tube placement, severe constipation are detected during regular patient care and documented in the medical record. Assessment according to trial criteria is done by investigators.

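### Withholding the block length does not make allocation unpredictable in this open, center-stratified trial; block lengths that vary at random would remove most near-certain predictions

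*Protocol article*

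**What the plan says.** All of this stands in the protocol article under Randomization and blinding, unless another section is named.

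- Method: "The randomization numbers will be allocated to the two groups in balanced permuted blocks and stratified by center".
- Purpose of the safeguard: "To avoid any potential of predicting the group allocation of future patients".
- The safeguard: "the block length is fixed in a separate document that is withheld from the study site". In addition, those who randomize "do not have the right to read or edit the randomization design chosen within the software".
- Openness: "Patients are not blinded and blinding of the surgeon is unfeasible".
- Software: "This software allows choosing different randomization methods as well as different sets of parameters for the chosen method". The parameters chosen are not stated.

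The text does not say that block lengths vary, nor expressly that a single length is used throughout. Under Subject exclusion criteria, one criterion is a judgement: "Expected lack of compliance". Table 1 places eligibility at visit 1 and randomization at visit 2.

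**The concern.** A balanced block must end with equal numbers in both arms. In an open trial a center sees every earlier allocation, so whoever keeps a count knows which arm is behind, and that arm is the likelier one next. This needs no knowledge of the block length. If the length is constant, the pattern of returns to balance also narrows down what it is, and some allocations then become certain.

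The stake is selection. Eligibility is settled before randomization and partly by judgement. Someone who foresees the next arm could enrol, defer or exclude a patient accordingly, and no later analysis fully corrects for that. The protocol relies on its safeguard to rule this out completely, so it matters whether the safeguard does so.

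**Working it through.** **The plan's own figure.** The protocol gives no figure for predictability. Its sample size enters only through center size. The values of alpha and power are missing from the text; I assume 0.05 two-sided and 90%. With rates of 14% and 3% (mean 8.5%):

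n = [1.960·√(2·0.085·0.915) + 1.282·√(0.14·0.86 + 0.03·0.97)]² / 0.11² = (0.773 + 0.496)² / 0.0121 ≈ 133 per group, as stated.

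Then 2·133 + 68 = 334 randomized. With about 20 centers, 334/20 = 16.7, so about 17 patients per center.

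**Assumptions.** Centers of equal size; one constant length of 4, 6 or 8; every earlier allocation in the center is visible.

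**Step 1: complete blocks, length known (upper bound).** For a block of length 2m:

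- Share of allocations fixed by the earlier ones = 1/(m+1): 1/3, 1/4 and 1/5, or 33%, 25% and 20% for lengths 4, 6 and 8.
- Share guessed correctly by naming the arm that is behind (ties count half) = [m + ½(4^m/C(2m,m) − 1)]/(2m). Length 4: [2 + ½(16/6 − 1)]/4 = 71%. Length 6: [3 + ½(64/20 − 1)]/6 = 68%. Length 8: [4 + ½(256/70 − 1)]/8 = 67%.

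Enumerating all blocks gives the same values.

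**Step 2: length withheld.** Let staff assume only that one of the lengths 2, 4, 6 or 8 is used, each equally likely at the start. For candidate length b, let a and c be the places left in the current block for arms A and B. Then P(next = A | b) = a/(a+c). Each candidate is weighted by how well it explains the sequence so far.

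Example: a center's first two patients are both in arm A. Length 2 is ruled out. The weights for 4, 6 and 8 are 1/6, 1/5 and 3/14, and the chances of B next are 1, 3/4 and 2/3. So P(B) = (0.167 + 0.150 + 0.143)/(0.167 + 0.200 + 0.214) = 0.79, with the length still secret.

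**Step 3: simulation of 17-patient centers.**

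| Scheme | Certain, length known | Certain, length withheld | Over 90% confidence, withheld | Guessed correctly, withheld |
|---|---|---|---|---|
| Constant 4 | 31% | 6–7% | 18% | 70% |
| Constant 6 | 21% | 7% | 14% | 66% |
| Constant 8 | 19% | 13% | 18% | 66% |

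Naming the arm that is behind gives the same 70%, 66% and 66%. With a constant length of 2, no allocation is strictly certain under these beliefs, but 74% are guessed correctly.

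**Step 4: lengths varying at random among 4, 6 and 8.** Even if staff know this set, about 2% of allocations are certain, about 4% are foreseen with over 90% confidence, and about 66% are guessed correctly.

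**Step 5: larger centers.** The share foreseen with over 90% confidence under a withheld constant length of 4, 6 or 8 is about 18% to 24% with 30 patients and 20% to 28% with 40. With the random mix it stays at about 4% to 5%.

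**The case against.** **A constant length is not stated.** The sentence can mean only that the length is specified in the separate document. That document is properly not public, and the software allows several parameter sets. This stands: a single constant length is the natural reading of the singular, not an established fact. It does not rescue the absolute claim, because random lengths also leave guessing at about 66%.

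**Secrecy does help.** It cuts certain predictions over 17 patients from 19–31% to about 7–13% for lengths 4 to 8. This stands too. A reader might infer that staff can predict every next allocation; they cannot. Some are certain and the rest are guessed better than chance. The 33%, 25% and 20% of Step 1 apply only if the length is known.

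**Other safeguards exist.** The design is unreadable to those who randomize, the randomizer's name and the date are stored, a screening log records reasons for exclusion, and monitoring verifies eligibility at least in part. These can deter or expose selective enrolment. They do not prevent counting, and the log need not show that a patient was merely deferred.

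**The harm is not demonstrated.** A reader might infer a biased primary result or an inflated type I error. The documents do not support a figure. Suppose half the patients are difficult with 16% risk, the rest have 4%, and the difficult share is steered to 75% against 25% at every certain allocation. The false risk difference is then 0.12 × 0.50 = 0.06 times the share certain, or about 0.4 to 0.8 points for shares of 7% to 13%. All these risks and the steering are assumed, so this is an illustration and not an expected effect. A reader might also infer that the same surgeons recruit, schedule randomization and operate; the article does not say so.

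**Conclusion.** The concern holds in limited form. The protocol claims that withholding the block length removes all potential for prediction, and in an open trial with center-stratified balanced blocks it does not. Under a withheld constant length of 4, 6 or 8 and 17 patients per center, roughly one allocation in six (14% to 18%) can be foreseen with over 90% confidence, and about two in three are guessed correctly against one in two by chance. Larger centers are generally more exposed. The sizes rest on equal centers, the assumed lengths and staff who keep a careful count.

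This is a weakness of concealment that can be reduced cheaply. It is not evidence that allocation was or will be abused.

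**What to change.** 1. Check the withheld document. If it already sets randomly varying lengths, only the wording in item 3 needs to change.
2. If it does not, set block lengths that vary at random within each center, for example 4, 6 and 8, for all allocations still to be made. Date and document the change.
3. Under Randomization and blinding, state: *Block lengths vary at random within center and are not disclosed to the sites.* Describe the purpose as to *reduce the predictability of* future allocations, in place of the absolute claim.

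The gain is in near-certain predictions: from about 7–13% to about 2% certain, and from about 14–18% to about 4% above 90% confidence. The overall correct-guess rate hardly moves, which is why the wording must change as well.

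Cost: a setting in software already in use, provided it can be changed while recruitment runs (the article says parameters can be chosen, not that they can be altered mid-trial); an amendment to a running allocation scheme; and slightly larger possible imbalance within centers. No patients, visits or staff are added.

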### Interventions

#### Treatment description

The following description of treatment is a recommendation and should be followed by all participating surgeons. Technique for hand-suture can be modified according to local standards. In contrast the stapling of an anastomosis must be performed as stated below.

#### Standardized mobilization of loop ileostomy

The operation is initiated with an oval skin incision around the ileostomy and temporarily closed by continuous suture to prevent further stool contamination. The loop ileostomy is then thoroughly mobilized from the subcutaneous layer and from the abdominal wall until it is loose and can be moved out of the peritoneal cavity.

#### Stapler group

The TLC-75-stapler (Ethicon, Norderstedt) is brought into the two opened antimesenteric apexes of the intestinal shanks to facilitate side-to-side (functional end-to-end) anastomosis (Figure 1). The apex of the loop and the spout is cross-stapled with a refill of the TLC-stapler followed by overstitching the cross-stapled line with a Polydioxanon equivalent suture (USP 5-0/Ethicon, Norderstedt). The intestine is then put back into the peritoneal cavity. The abdominal wall is closed with interrupted sutures using Polyglactin equivalent sutures (USP 2). The subcutaneous tissue is not sutured and no subcutaneous drainage is used. The skin can be closed by either interrupted monofilament sutures or clips.

**Figure 1 F1:**
[figure not shown]
**Stapled side-to-side anastomosis before (a) and after (b) stapling**.

#### Hand-suture group

After thorough mobilisation the loop ileostomy is resected using two bowel clamps. An end-to-end anastomosis is performed as follows: a two-layer continuous suture using four Polydioxanon equivalent sutures (USP 5-0). The inner layer consists of a transmural suture, the outer layer of a sero-muscular suture. Alternatively, interrupted sutures may be performed depending on local standards. The abdominal wall and the skin are closed in the same way as for stapled closure.

#### Permitted and not permitted medication(s)/treatment(s)

No other method of ileostomy than the randomized and described technique in the protocol should be used for anastomosis. Any protocol violation has to be reported with a clear description.

The postoperative care is performed according to the principles and standard of the department.

### Outcomes (primary and secondary)

The primary endpoint is the occurrence of bowel obstruction within 30 days after ileostomy closure.

#### Assessment of the primary endpoint

Bowel obstruction is defined as productive vomiting or the need of gastric tube placement or absolute constipation with a duration of at least three days. This definition is based on the existing trial by Hasegawa [9] which provides the data for sample size calculation of the HASTA-Trial.

Secondary endpoints are the time needed to perform the procedure, wound infection, rate of re-operation due to anastomotic leakage of the ileostomy closure, time to first tolerance to solid food and first bowel movement, whichever of these occurred last, length of postoperative hospital stay, 30 days and 12 months mortality after ileostomy closure, rate of re-operation and re-hospitalization within one year due to bowel obstruction, costs of surgical procedure for the institution (including threads, stapler, time etc.), quality of life (EuroQol 5 D).

Three out of, five visits are documented by the investigator in each center during in hospital phase (screening, intervention and discharge), followed by two telephone interviews for 30 days and 12 months follow up after operation (Table 1 and Figure 2).

**Table 1 T1:** Course of examinations

Visit	1 (=Screening)	2 (Operation)	3 (day of discharge)	4 (30 days post OP)	5 (12 ± 1 months post OP)
Demographics and baseline clinical data	X				

Eligibility criteria	X				

Randomization, Surgical intervention		X			

Clinical visit/Follow-up			X	X	X

Quality of life (EuroQol 5 D)	X			X	X

Safety		X	X	X	X

**Figure 2 F2:**
[figure not shown]
**Flowchart**.

### Data management and monitoring

#### Documentation

All protocol-required information collected during the trial must be entered by the investigator, or designated representative, in the case report form (CRF). A paper based CRF is used to collect the data. The investigator, or designated representative, should complete the CRF pages as soon as possible after information is collected, preferably on the same day that a trial subject is seen for an examination, treatment, or any other trial procedure. Any outstanding entries must be completed immediately after the final examination. An explanation should be given for all missing data.

The completed CRF must be reviewed and signed by the investigator named in the trial protocol or by an authorized sub-investigator. To ensure that the database reproduces the CRF correctly, the Institute of Medical Biometry and Informatics Heidelberg (IMBI) accomplishes a double entry of data. Completeness, validity and plausibility of data are examined by validating programs, which thereby generate queries. The investigator or the designated representatives are obliged to clarify or explain the queries. At the end of the trial, the principal investigator will retain the originals of all CRF.

The data will be managed and analyzed in the joint unit of SDGC and IMBI in accordance with the appropriate standard operating procedures (SOP).

#### Trial monitoring

Monitoring is carried out in accordance with ICH E6 (GCP) and standard operating procedures of the Coordinating Centre for Clinical Studies (KKS) Heidelberg. Two different monitoring strategies are used within as the HASTA trial is part of the ADAMON project (Prospective cluster-randomized study of trial-specific adapted strategies for on-site monitoring in combination with additional quality management measures [11]), which is funded by the German Federal Ministry of Education and Research (BMBF, 01 EZ 0876).

#### Risk-adapted monitoring strategy

Half of the trial centers, chosen at random, are monitored by a risk-adapted monitoring strategy which is described in a trial specific monitoring manual. Participating centers are activated with an initiation visit by the monitor, who will hand-out the prepared investigator site file. All relevant trial issues are discussed and personnel are trained on trial specific procedures, documentation and web-based randomization. The monitor is in regular contact by phone or e-mail with all participating centers to follow progression of the study, protocol adherence, and to discuss trial related problems. Further monitoring visits are carried out during the course of the trial for source data verification of relevant core data, i.e., patient informed consent, inclusion/exclusion criteria, performed treatment, primary and secondary endpoints and serious adverse events. Frequency of regular monitoring visits depends on the number of recruited patients and the performance of each trial center. Every trial center is visited at least once during the trial. Close-out visits are not as a standard foreseen in the centers.

#### Full monitoring

The remaining participating centers will be monitored by a "full" or 100% monitoring (control-intervention for ADAMON) including: initiation visit, first regular monitoring visit (after inclusion of first patient), further regular monitoring visits (after inclusion of 8 additional patients or every 6 months, if new patients have been recruited), 100% source data verification for all included trial patients, close-out visit.

In addition, an efficient central supervision of the clinical trial is established (central monitoring) for both strategies. Investigators in the participating centers will support the monitor in his/her activities.

